### Recruitment, study procedures and assessments

Participants will be recruited from the large cohort of FAP patients at the hereditary GI Cancer clinic at the Amsterdam UMC. Prior to their routine surveillance colonoscopy, patients will be invited to participate by a member of the study team. In total 12 patients will be included in this trial. For all patients, lithium will be administered for a period of six months, between month 6 and 12. Since every participant is given the same treatment, no randomization will take place.

During the course of the study, four colonoscopies (at t = 0 months, t = 6 months, t = 12 months, t = 18 months) will be performed to evaluate the effect of lithium on clone sizes and stem cell dynamics in mucosal biopsies and total adenoma burden. Physical examination (including vital signs) will be performed at baseline and every six months, at time of endoscopy. Laboratory testing will be performed at baseline and every two months from start of lithium treatment. Serum lithium levels will be measured at day 12 and day 22 after start of treatment. When the therapeutic range is reached, serum levels will be measured once a month. Blood samples for determining serum levels must be collected 12 h after oral administration of lithium. If necessary, dose adjustments will be made by the investigator based on serum levels, laboratory tests and side effects. Serum lithium levels will be monitored 12 days after dose adjustments, until the therapeutic range is reached or side-effects diminished. Further check-ups will be performed through telephone interviews to evaluate AE’s and side effects using a lithium side effect questionnaire base on a previously designed tool [20]. A schedule of activities is included in the supplementary materials (Additional file 2: Schedule of activites). More detailed information on study visits, follow-up, data monitoring, safety reporting and auditing is included in the study protocol and clinical trial registry records [21].

#### Assessment of size of fixed clones

For each patient, crypts will be retrieved from biopsies of normal mucosal tissue taken at colonoscopy. *APC*-mutant stem cell dynamics will be determined in these biopsies by tracing the spread of the *APC-*mutant cells using specific expression of *NOTUM* by RNAscope (in situ hybridization). *NOTUM*-positive crypts will be quantified by determining the proportion of the crypt circumference positive for *NOTUM* (in parts of eight, 1:8 to 8:8). This will result in an average clone size distribution for each patient per time point, as well as the proportion of fixed crypts (8:8). By analyzing the differences in clone size distribution before, during and after lithium treatment we aim to observe a relative reduction in average clone size of 50% during the lithium treatment, as well as a reduction in crypt fixation of 50%.

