## Objectives

### Primary objective

The primary objective of this study is to evaluate the effect of low-dose lithium on the spread of *APC*-mutant cells within intestinal crypts of FAP patients over time. This will be assessed by using an *APC* mutation specific marker (*NOTUM*) and is defined as a significant reduction of fixed crypts and reduction of fixed clone size by 50%.

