### Data analysis

All *NOTUM* + clone size analysis data and adenoma counts will be scored blindly. To describe the study population, baseline characteristics and changes in outcome parameters during follow-up, descriptive statistics will be used in this study. SPSS for Windows software (Chicago, IL, USA) version 26.0 will be used for these analyses. If other statistical analysis will be used, this will be mentioned in the study paper. Primary analysis for the primary outcome parameter will be done by analyzing the data using two-sided student’s t-test. The limit for the statistical significance will be established at *p* < 0.05 with a confidence interval of 95%. Descriptive statistics will be used to describe the changes in secondary outcome measures during follow-up.

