### Sample size calculation

Simulations of clonal expansion in the intestine indicate that in order to detect a reduction of 50% (power stat. 80%, *p* = 0.05) in fitness of *APC*-mutant cells, we need to analyze sizes of *APC* mutant clones within 11 partially populated crypts at 4 time points in 12 individuals. To ensure sufficient material we need 840 crypts per patient per time point. A typical biopsy yields 100–250 crypts, therefore we will perform 12 biopsies in total (2 biopsies per segment, 6 segments) per patient per time point. In that way, sufficient data will be obtained to confirm or refute the study hypothesis.

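### The 80% power does not cover the primary objective as defined: it requires a 50% reduction in clone size, while the planned test needs only p < 0.05 and the power refers to mutant-cell fitness

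*Protocol article*

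**What the plan says.** Four sections of the protocol article bear on what counts as a positive result.

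- **Primary objective.** The effect on the spread of mutant cells "is defined as a significant reduction of fixed crypts and reduction of fixed clone size by 50"%. Significance (on fixed crypts) and magnitude (on clone size) are joined by *and*.
- **Assessment of size of fixed clones.** Here the investigators aim to see a "relative reduction in average clone size of 50% during the lithium treatment, as well as a reduction in crypt fixation of 50"%. This puts 50% on both measures, but as an aim.
- **Data analysis.** The primary outcome is analysed "using two-sided student’s t-test". "The limit for the statistical significance will be established at" p < 0.05, with a 95% confidence interval. No minimum observed reduction appears.
- **Sample size calculation.** Simulations were used "in order to detect a reduction of 50"% (80% power, p = 0.05) "in fitness of *APC*-mutant cells", based on 11 partially populated crypts at 4 time points in 12 individuals. The section closes: "In that way, sufficient data will be obtained to confirm or refute the study hypothesis".

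**The concern.** The figure of 50% does two jobs. In Sample size calculation it is an assumed true effect that the trial should be able to detect. In Primary objective it is part of the definition of the result. These are different demands. Power of 80% is the chance that a test reaches p < 0.05. It is not the chance that the observed reduction is at least as large as the assumed one.

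The consequence is that the same data could be read in opposite ways. Suppose fixed crypts fall significantly and clone size falls by 45% with p < 0.05. Under Data analysis the trial is positive. Under Primary objective it has missed its definition. In a 12-patient single-arm study offered as proof of concept, that should be settled before results are known.

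**Working it through.** **1. The plan's own figure.** The 12 patients and 80% power come from clonal-expansion simulations. The article does not give their inputs (baseline fitness, number of stem cells, between-patient variation), so the figure can be neither reproduced nor refuted. A condensed article may leave such inputs out, and that is not the point here.

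**2. What the 80% refers to.** Side by side:

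| Section | Quantity | Condition |
|---|---|---|
| Primary objective | fixed crypts | significant |
| Primary objective | clone size | reduction of 50% |
| Assessment of size of fixed clones | average clone size; crypt fixation | aim of 50% on each |
| Data analysis | primary outcome | p < 0.05 only |
| Sample size calculation | fitness of mutant cells | 80% power to detect 50% |

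The power row matches none of the others in quantity, and it contains no observed threshold.

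**3. Chance of observing at least 50% when the truth is 50%.** For an estimate distributed symmetrically around a true reduction of 0.50, P(estimate ≥ 0.50) = 0.50. No SD is needed.

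**4. A stand-in, to give scale.** Assume a paired two-sided t-test on the measured reduction, with n = 12, α = 0.05 and 80% power at a true reduction of 0.50. (The article does not say whether the test is paired.)

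- Standardized effect d solving P(T > 2.201) = 0.80, with T noncentral t on 11 df and noncentrality d√12: d = 0.889.
- Implied SD = 0.50/0.889 = 0.563. SE = 0.50/(0.889 × √12) = 0.162.
- Smallest significant observed reduction = 2.201 × 0.162 = 0.357, about 36%. The normal approximation gives SE = 0.50/(1.960 + 0.842) = 0.178 and 1.960 × 0.178 = 0.35.
- P(observed ≥ 50%) = 1 − Φ((0.50 − true)/0.162):

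| True reduction | P(observed ≥ 50%) |
|---|---|
| 30% | 11% |
| 40% | 27% |
| 50% | 50% |
| 60% | 73% |
| 70% | 89% |

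- True reduction needed for an 80% chance: 0.50 + 0.842 × 0.162 = 0.637, about 64%.
- Simulation of 400,000 trials at a true 50%: power 0.801; observed ≥ 50% in 0.501; observed ≥ 50% and significant in 0.499.

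**5. The Primary objective as worded.** Require clone size ≥ 50% (true value 50%) and significance on fixed crypts (80% power assumed), with bivariate normal estimates of correlation ρ:

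- ρ = 0: 0.50 × 0.80 = 0.40
- ρ = 0.5: 0.46
- ρ = 0.9: 0.498

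The upper bound is 0.50.

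**6. From fitness to the measured endpoint.** As an illustration, take biased drift with N stem cells and replacement probability P. Fixation probability is (1 − g)/(1 − g^N), with g = (1 − P)/P. For N = 7 and P = 0.7 it is 0.573. Halving the excess over neutral (P = 0.6) gives 0.354, a reduction of 1 − 0.354/0.573 = 38%. Over assumed ranges N = 5 to 8 and P = 0.6 to 0.8, the reduction in fixation is:

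- 25–39% if the excess replacement probability is halved
- 19–31% if the selection coefficient is halved
- 31–89% if the fitness ratio is halved

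A 50% loss of fitness therefore need not be a 50% fall in fixation, and may lie on either side of it.

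**The case against.** The strongest reply is that 50% is only the hypothesised effect. The assessment section says the investigators aim to observe it, and Data analysis, which governs the primary test, asks only for p < 0.05. On that view there is no threshold and nothing to power for. This is right about the assessment section: it states an aim and should not be read as a pass/fail rule. Treating it as one would give 25% (ρ = 0) to 43% (ρ = 0.9) for both measures reaching 50%, but the text does not make it one. Independence is also implausible, because both measures come from the same crypts and a fixed crypt is the top category of the same scale. The reply does not dispose of Primary objective, which uses the language of definition and joins the 50% to significance.

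A second reply also stands: every SE above is back-calculated. The 36% and 64% figures illustrate a stand-in test and are not properties of the trial's simulation.

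A third is that a minimum observed effect is a legitimate choice in a proof-of-concept phase II trial. That is true, but then the probability of meeting it should be stated.

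**Conclusion.** The success criterion differs between Primary objective, the assessment section and Data analysis. The power statement covers a fourth quantity and no observed threshold. The 80%, and the closing claim that the data will decide the hypothesis, therefore do not apply to the objective as defined. If the true reduction in clone size is exactly 50%, the chance of observing at least 50% is about one half. It is about 40–50% if fixed crypts must also be significant.

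These figures assume a roughly symmetric unbiased estimator, 80% power on fixed crypts, and ρ from 0 to 0.9. They also read the objective's clone size as the average clone size of the assessment section, since a fixed crypt is 8:8 by definition.

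Two stronger conclusions are tempting and are not supported:

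- **That success at the design effect is at most 50% instead of 80%.** The design effect is in fitness, the threshold is on clone size, and no conversion is given. By step 6 the chance at a halved fitness could be well below or above 50%.
- **That the decision on a larger trial rests on a coin flip.** The Discussion links a larger trial to reduced NOTUM expansion and acceptable safety, with no 50% threshold. A significant 45% reduction would satisfy its efficacy part.

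**What to change.** - In Primary objective and in Assessment of size of fixed clones, define success as a significant reduction by the planned two-sided test (p < 0.05) on one named primary parameter, reported with its estimate and 95% CI. Remove 50% as part of the definition.
- In Sample size calculation, keep 50% as the design assumption and say which quantity it refers to. If that remains fitness, say how it relates to the parameter tested.
- If an observed 50% threshold is kept, say that the 80% does not cover it, and give the probability of meeting it on the tested endpoint (about 50% if the true reduction on that endpoint is 50%). Restrict the closing sentence of that section accordingly.

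The cost is modest. No patients, visits or biopsies are added. The sponsor must choose between clone size and the proportion of fixed crypts as the named parameter, which the text has not yet done. The claim after a positive result becomes a reduction, with its size carried by the confidence interval.

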#### Assessment of adenoma burden

A full colonoscopy will be performed at baseline, and at months 6, 12 and 18 to assess adenoma burden and to take biopsies. During colonoscopy, Boston Bowel Preparation Scale (BBPS) should be 2 for each segment and cecal intubation achieved. Adenoma burden will be assessed by estimating the number and size (estimated using a biopsy forceps) of adenomas in each of the 6 colorectal segments: cecum, ascending colon, transverse colon, descending colon, sigmoid and rectum (including retroflexion). For each colonoscopy, the table below will be used to calculate the sum of diameter of adenomas to determine the total colorectal adenoma burden (Table 1). Standard white light endoscopy (WLE) will be used; Narrow band imaging (NBI) is used at the discretion of the endoscopist. Adenomas ≥ 5 mm should be excised at all colonoscopies. At each endoscopy, also two random biopsies of normal mucosa will be taken in each segment, resulting in a total of 12 biopsies of normal intestinal mucosa. Video recordings will be made for all colonoscopies (only using WLE). All four videos of each participant will be reviewed by two separate independent expert endoscopists in a random order, assessing the adenoma burden using the table below. If there is a disagreement of more than 30% in the adenoma burden assessment between the two reviewers, a third independent reviewer will be engaged. Then, the average of these three reviewers will be used for further analysis.

**Table 1 Tab1:** Total adenoma burden

Segment	Number of adenomas			
	1–2 mm	3–5 mm	6–10 mm	> 10 mm
Cecum				
Ascending colon				
Transverse colon				
Descending colon				
Sigmoid				
Rectum				
Total adenoma burden				

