### Secondary objectives

To evaluate:The effect of low-dose lithium on number of adenomas and size, determined as sum of diameter of all adenomas;Side effects of low-dose lithium in FAP patients, evaluated by lithium side effects questionnaires;The safety of low-dose lithium in FAP patients, evaluated by adverse events, findings during physical examination and laboratory tests.

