#### Secondary outcomes

Secondary endpoints include:Difference in number and size of adenomas, determined as sum of diameter of all adenomas between baseline and end of study;Patient reported side-effects of low-dose lithium in FAP patients, using a lithium side effect questionnaire (Additional file 1: Lithium side effect questionnaire);Safety outcomes of low-dose lithium by analyzing adverse events, physical examination and laboratory findings including hemoglobin, thrombocytes, leukocytes, GFR, creatinine, urea, sodium, potassium, calcium TSH (if deviating T4), urine osmolality and creatinine.

Given the fact that dietary factors can influence intestinal stem cell dynamics, we also aim to monitor the following parameters: number of cups of coffee per day (decaffeinated coffee not included); turmeric use (gram per day); number of fish oil capsules per day (amount of eicosapentaenoic acid in terms of mg) and history of smoking (if yes number of pack years).

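### Table 1 gives only an approximate sum of adenoma diameters, because no value per size bin is fixed, and its 3–5 mm bin straddles the 5 mm excision limit

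*Protocol article*

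**What the plan says.** The Secondary objectives section of the protocol article covers adenoma number and size, with size "determined as sum of diameter of all adenomas". The Secondary outcomes section makes this a comparison over time: "Difference in number and size of adenomas, determined as sum of diameter of all adenomas between baseline and end of study".

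The section Assessment of adenoma burden describes the measurement as "estimating the number and size (estimated using a biopsy forceps) of adenomas in each of the 6 colorectal segments". It then names Table 1 as the instrument: "the table below will be used to calculate the sum of diameter of adenomas to determine the total colorectal adenoma burden (Table 1"). As printed, Table 1 has one row per segment under the column heading "Number of adenomas", split into 1–2, 3–5, 6–10 and > 10 mm, and a bottom row for total adenoma burden. It has no field for a diameter, and the text assigns no diameter to a bin. The video readers use the same form: recordings are "reviewed by two separate independent expert endoscopists in a random order, assessing the adenoma burden using the table below".

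The same section states that "Adenomas ≥ 5 mm should be excised at all colonoscopies". There are four colonoscopies, at months 0, 6, 12 and 18. The Study population section says that patients serve as their own controls.

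**The concern.** The instrument and the endpoint do not match. A table of counts gives a sum of diameters only after each bin is given a value. The article fixes none, and the > 10 mm bin has no natural one. If the values are settled after data are seen, the size endpoint depends on a choice that could have been made beforehand.

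The second mismatch matters more for interpretation. Removing lesions at one colonoscopy lowers the burden at the next, whatever lithium does. To read a within-patient change, one needs to know how much of the earlier burden was due for removal. The bin edge falls between 5 and 6 mm, while the excision limit falls between 4 and 5 mm, so the form cannot say.

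Third, lesions left in place are 1–4 mm and fall in only two bins. A change from 1 to 2 mm or from 3 to 4 mm, in either direction, leaves the form unchanged.

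**Working it through.** The article gives no numerical sum of diameters, so there is no figure to reproduce. The bins and the excision limit come from Assessment of adenoma burden. The following are assumptions: whole-millimetre readings; 100 adenomas (the main inclusion minimum) split 50/40/8/2 over the four bins; top bin 11–20 mm.

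**Bounds on the sum (count × smallest or largest diameter in the bin)**

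- Lower: 50×1 + 40×3 + 8×6 + 2×11 = 50 + 120 + 48 + 22 = 240 mm
- Midpoints: 50×1.5 + 40×4 + 8×8 + 2×15.5 = 75 + 160 + 64 + 31 = 330 mm
- Upper: 50×2 + 40×5 + 8×10 + 2×20 = 100 + 200 + 80 + 40 = 420 mm

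The ratio is 420/240 = 1.75. Other assumed mixes behave alike: 70/30/0/0 gives 160–290 mm (1.81) and 60/30/10/0 gives 210–370 mm (1.76). The width therefore does not depend on having lesions > 10 mm. Where there are such lesions and no cap, there is no upper bound.

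**Random variation within bins.** If sizes are independent and uniform over the whole millimetres of each bin, the per-lesion variances are 0.25, 0.667, 2 and 8.25.

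- SD = √(50×0.25 + 40×0.667 + 8×2 + 2×8.25) = √71.7 ≈ 8.5 mm
- 8.5/330 ≈ 2.6%

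The 240–420 mm range is therefore a worst case in which every lesion lies at the same end of its bin. It is not a likely error.

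**Excision.** Let k of the 40 lesions in the 3–5 mm bin measure 5 mm. Lesions due for excision number 10 + k, which is anything from 10 to 50 of the 100. Their diameter within that bin is 5k, from 0 to 200 mm. Now score by midpoints and suppose that removal is the only change before the next colonoscopy. The sum falls from 330 to 75 + 4×(40 − k) = 235 − 4k:

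| k | Next sum (mm) | Fall from 330 mm |
|---|---|---|
| 0 | 235 | 28.8% |
| 13 | 183 | 44.5% |
| 40 | 75 | 77.3% |

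The starting table is identical in all three rows, so it cannot show what fall to expect from removal alone. The extremes are limits, not predictions.

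**Unseen change in small lesions.** If 50 lesions shrink together from 2 to 1 mm, the true sum falls by 50×1 = 50 mm and the table does not change. The same holds for 4 to 3 mm.

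**What the revised form would leave.** The present width of 420 − 240 = 180 mm is made up of 50 + 80 + 32 + 18 mm over the four bins. With individual estimated diameters from 5 mm upward, only the 1–2 and 3–4 mm bins remain uncertain: 50×1 + (40 − k)×1 = 50 to 90 mm.

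**The case against.** A reader might infer that the sum of diameters cannot be calculated at all. The documents do not support that: counts multiplied by a fixed value per bin give an approximate sum, and the full protocol, which is not shown, may set such values. If an unstated constant were the only gap, this would be detail that an article may leave out. What stands is that the article prints the form, says the sum is calculated from it, and places the bin edge off its own excision limit.

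A reader might also take the 1.75-fold range as the expected error. It is a worst case. One fixed rule applied at every visit also cancels in part: if only the ten larger lesions disappear, the fall is 70/240 = 29.2% at bin minima, 95/330 = 28.8% at midpoints and 120/420 = 28.6% at maxima.

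Examples such as 5 mm shrinking to 3 mm, or 10 to 6 mm, are tempting but do not fit the plan, because such lesions are to be excised. The valid examples lie below 5 mm.

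Nor do the documents show that excision can never be accounted for. Colonoscopies are video-recorded and excised tissue is stored, and nothing makes Table 1 the only record. The statement here is narrower: Table 1 cannot do it.

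Finally, coarse bins are defensible. The Discussion acknowledges how hard it is to quantify up to a thousand adenomas from video, adenoma number can be read from the form directly, and the straddling affects only lesions read as 5 mm on a visual estimate. These points limit the importance of the finding. They do not explain why the bin edge and the excision limit differ.

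**Conclusion.** The point holds in limited form. Table 1 supports an approximate sum of diameters whose level depends on bin values that the article does not state: 240–420 mm at worst on the assumed mix, with random variation of about 2.6% around 330 mm. Its 3–5 mm bin mixes lesions due for excision with lesions left in place. On the same mix, the fall to be expected from removal alone could lie anywhere between about 29% and 77%, and the form cannot narrow this. Changes within the 1–2 mm range, or between 3 and 4 mm, are not recorded.

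These figures rest on an assumed size mix, an assumed 20 mm cap and whole-millimetre readings. A reader might infer that the trial's main result is at risk, but the documents do not support that. Adenoma burden is a secondary outcome, the Data analysis section plans only descriptive statistics for it, and the primary NOTUM outcome and the sample size do not depend on it. The change is still worth making because it is cheap and the comparison is within patient. No position is taken on the excision limit itself.

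**What to change.** Revise Table 1 before first use:

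1. Align the bin edge with the excision limit already stated: 1–2, 3–4, 5–10 and > 10 mm.
2. Record the individual estimated diameter of each lesion of 5 mm or more. This removes the open-bin problem and shows the burden due for removal separately from the burden left in place.
3. Fix in advance the value for each small-lesion bin, for example 1.5 mm for 1–2 mm and 3.5 mm for 3–4 mm, and state the sum as small-lesion counts times these values plus the recorded diameters.

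The cost is a new form and slightly more recording time for the endoscopists (12 patients × 4 = 48 colonoscopies) and for the video readers (48 × 2 = 96 readings, more where a third reader is needed). If colonoscopies have already been scored, the recordings may allow re-scoring. The change does not fully cure the insensitivity below 5 mm, since 1 to 2 mm and 3 to 4 mm still go unseen. Nor does it remove the effect of excision on later burden: it only lets that effect be described.

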### Study population

Patients diagnosed with FAP, between the age of 18 and 35, with intact colons/rectums, are eligible for this study. No exclusion will be made based on sex or race. For this study no control group will be included, but patients serve as their own control in the non-treatment phase.

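### Adenomas of 5 mm or more are excised at every colonoscopy, but the adenoma-burden endpoint is an uncorrected baseline-to-end difference, so excision pushes it down whatever lithium does

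*Protocol article*

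**What the plan says.** In the protocol article, Assessment of adenoma burden sets four colonoscopies: "A full colonoscopy will be performed at baseline, and at months 6, 12 and 18 to assess adenoma burden". Adenomas of at least 5 mm "should be excised at all colonoscopies". Burden is obtained from Table 1, which counts lesions by segment and by size (1–2, 3–5, 6–10 and over 10 mm): "the table below will be used to calculate the sum of diameter of adenomas to determine the total colorectal adenoma burden". The table has no entry for lesions removed at an earlier visit.

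Secondary outcomes defines the endpoint as "Difference in number and size of adenomas, determined as sum of diameter of all adenomas between baseline and end of study". Data analysis handles it without a test: "Descriptive statistics will be used to describe the changes in secondary outcome measures during follow-up".

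Under Recruitment, study procedures and assessments, "lithium will be administered for a period of six months, between month 6 and 12". There is no control group; Study population states that "patients serve as their own control in the non-treatment phase".

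**The concern.** A sum of diameters gives most weight per lesion to the largest lesions, and those are the ones taken out. Three rounds of removal (months 0, 6 and 12) lie between the baseline reading and the month-18 reading, and two of them (months 0 and 6) come no later than the start of lithium. A concurrent control arm would share the excision effect and cancel it. A before-and-after comparison in one arm cannot. Blinded video review in random order guards against reader bias, but it cannot restore lesions that are physically gone.

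This is the trial's only efficacy outcome on adenomas, and the Discussion counts on the endoscopic measurements for clinical information alongside the translational result. As defined, the measure cannot separate lithium from polypectomy.

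**Working it through.** The article gives no effect size, standard deviation or power for adenoma burden, so there is no stated figure to reproduce. The 12 patients are justified on the primary endpoint only.

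**Direction.** Let B0, B6, B12 and B18 be the burdens seen before excision at each visit, and E0, E6 and E12 the diameters excised at the first three. The stated endpoint is B18 − B0. Measuring each interval from what was left behind gives

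- months 0–6: B6 − (B0 − E0)
- months 6–12: B12 − (B6 − E6)
- months 12–18: B18 − (B12 − E12)

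These add up to B18 − B0 + E0 + E6 + E12. The stated endpoint is therefore lower than the accumulated interval change by exactly the diameters removed. The same identity holds for counts.

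**Size of the baseline removal (illustration).** The article gives no size distribution. Assumptions: 100 adenomas, mean 2.5 mm for those under 5 mm and 7 mm for those of 5 mm or more. The percentages do not depend on the number of adenomas, so they apply equally to patients entering with 50.

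| Share ≥ 5 mm (= share of count removed) | Calculation | Share of sum of diameters removed |
|---|---|---|
| 2% | 2×7 / (98×2.5 + 14) = 14/259 | 5.4% |
| 5% | 5×7 / (95×2.5 + 35) = 35/272.5 | 12.8% |
| 10% | 10×7 / (90×2.5 + 70) = 70/295 | 23.7% |
| 20% | 20×7 / (80×2.5 + 140) = 140/340 | 41.2% |

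A second set of assumed diameters (1.5, 3.5, 5, 8 and 12 mm) gives similar results for shares of 5%, 10% and 20%: 34/226.5 = 15%, 72/267 = 27% and 144/324 = 44%.

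**Net change over 18 months with no drug effect.** The second set of diameters was carried forward with assumed growth of 0 to 1 mm per year and 0 to 40% new adenomas per year, in 48 combinations.

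- Excision lowered the 18-month change by about 15 to 54 percentage points in every combination. The extremes can be checked by hand as (excised diameters + growth those lesions would have had) / baseline. Lowest: 34/226.5 = 15%. Highest: (144 + 20×1×1.5)/324 = 174/324 = 54%.
- Uncorrected burden was below baseline at month 6, before any lithium, in about 41 of 48 combinations. At month 18 it was below baseline in about half.
- Adding back the excised diameters came within 0 to 10 points of the no-excision change. Example (10% of lesions ≥ 5 mm, growth 0.25 mm per year, 10% new per year): uncorrected −7%, add-back +20%, no excision +21%. The remaining gap is the growth the removed lesions would have had.

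One limit of this model: its largest retained size is 3.5 mm, which at 1 mm per year is only 4.5 mm by month 12. Nothing therefore crosses 5 mm in time for the later excisions, and the figures reflect the baseline removal alone. Any removals at months 6 and 12 would come on top.

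**The case against.** Five points can be made on the other side.

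1. **Net fall.** A reader might infer that the sum of diameters must fall below baseline with no drug effect. The documents do not support that. Growth and new adenomas are not given, and in about half the assumed combinations burden still rose by month 18, though by less than it would have without excision.

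2. **Unequal bias between intervals.** A reader might also infer that the baseline excision clears a stock built up over years, so that the bias differs between intervals and works against lithium when months 0–6 serve as control. That is unsupported too. Participants come from a clinic cohort approached before routine surveillance colonoscopy, and earlier clearing is possible. The article does not say.

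3. **A condensed article.** The full protocol may log excised lesions and derive an adjusted burden. That is possible, but the article does more than stay silent: it fixes the measure, the two time points and the excision rule, and taken together as written they give a biased contrast.

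4. **Order of scoring and excision.** The article does not say that burden is scored before excision. If it were always scored after, the baseline removal would drop out of the contrast, but removals at months 6, 12 and 18 would enter it. The direction would stay the same; the baseline percentages above would not apply.

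5. **Limited consequence.** The endpoint is secondary and descriptive, and the Discussion ties a larger trial to NOTUM expansion and safety. This stands, and it limits the weight of the point.

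**Conclusion.** The point holds as a bias in direction. Mandatory excision combined with an uncorrected baseline-to-end difference in a single arm pushes measured adenoma burden down relative to no excision, irrespective of lithium. The direction follows from the text alone, provided at least one qualifying lesion is removed within the contrast.

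The size rests on assumption. With 2% to 20% of adenomas at 5 mm or more and mean diameters of 2.5 and 7 mm, the baseline excision takes about 5% to 41% of the sum of diameters and 2% to 20% of the count, so the count is the less affected measure. Whether burden ends below baseline, and whether the bias differs between intervals, cannot be settled from the article.

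The primary endpoint uses biopsies of normal mucosa and is not touched. The sponsor should correct this, but it does not threaten the main conclusion of the trial.

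**What to change.** Leave the excision rule as it is and change the measurement and the derivation.

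1. At every colonoscopy, record number, segment and diameter of each excised lesion, and state that burden is scored before excision.
2. Define change for months 0–6, 6–12 and 12–18 as burden before excision at the visit minus the residual burden after excision at the previous visit. For the baseline-to-end contrast, add back the lesions excised at months 0, 6 and 12; this is the same quantity summed. Do this for both count and sum of diameters.
3. Split the 3–5 mm class of Table 1 at the excision threshold. At present it mixes 5 mm lesions, which are excised, with smaller ones that are kept, so lesions under 5 mm cannot be read from the table. With the split, report change in lesions under 5 mm as a sensitivity analysis.

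The cost is a slightly longer case report form, a changed reader form and one derived variable. There are two drawbacks. Excised sizes logged by the endoscopist are combined with burden read from video, so two measurement sources are mixed, and this should be stated in the report. The add-back also omits growth that removed lesions would have had, which in the illustration leaves a gap of at most 10 points.
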